## Methods and analysis

### Study design and locations

We will conduct a multisite two-armed cluster randomised controlled trial using a nested cross-sectional design. The clusters are defined as schools and classes within schools. The study locations are spread across four world regions and include the cities of Fez, Morocco; Jaipur, India; Saint Catherine Parish, Jamaica; and Sekondi-Takoradi, Ghana. These locations (secondary cities) were purposefully selected in collaboration with WHO regional focal points to generate information for settings that are less likely to be in the focus or receive resources for adolescent health interventions.

In each city, approximately 30 schools will be selected and randomly assigned to either the intervention or control group. At baseline, all sampled schools will conduct a G-SHPPS to assess school policies and practices^14^ and a GSHS to assess risk behaviours and protective factors among students.^15^ Additionally, in the control group of each city, we will conduct studies to validate GSHS physical activity questions against an accelerometer (Axivity AX3^25^) to be worn by students on the wrist for 8 days prior to the baseline survey.

Following the baseline surveys, the intervention schools will participate in data-to-action workshops to develop a package of interventions. Students, parents, teachers, local authorities and researchers will work together to find and prioritise policy and programme solutions to establish a unified action plan. Subsequently, these interventions will be implemented, and study processes and outcomes will be assessed for differential change via repeat G-SHPPS and GSHS surveys after a 2-year follow-up. At follow-up, new classes will be selected from the same schools to ensure participation of 13–17 years old students similar in age to the baseline sample. We hypothesise that the prevalence of behavioural risk factors would be lower and the prevalence of protective factors higher among students in schools in the intervention group compared with the control group at follow-up. An overview of our study design is shown in figure 1.

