### Study population and sampling

This study’s target population is 13–17 years old students. In each city, following standard G-SHPPS and GSHS sampling procedures,^14 15^ approximately 30 schools will be randomly selected from a list of schools including every school in the city with eligible classes (classes that the target population usually attends), provided by education authorities from the respective cities. Selection will be done by experts from WHO with probability proportional to the number of students in the eligible schools.

For the GSHS, in a second sampling stage, classes will be randomly selected from all eligible classes. All students of selected classes will be asked to participate in the survey.

The city sample size was calculated to test the hypothesis that the prevalence of behavioural risk factors would be lower among students in the schools of the intervention group versus those in the control group at follow-up using G*Power V.3.1.^26^ With most outcome variables (prevalence of behavioural risk and protective factors) being binary, logistic regression was selected as the statistical test, the required power level was set at 80% and the significance level prespecified at α=0.05. The to-be-detected effect was specified at an OR=0.75, which represents the average of pooled effect sizes from a recent meta-analysis^11^ considering universal school interventions across a range of behaviours, similar to the ones assessed in our study.

The initial sample size calculation resulted in n=473, which was inflated assuming a design effect of 1.5 and an expected response rate of 90%: 473×1.5/0.9=788. Finally, this sample size was quadrupled aiming at reporting for two age groups within both the intervention and control arm: 13–15 and 16–17 years, resulting in a target sample size of n=3153.

Participation in the G-SHPPS and GSHS is voluntary. For the GSHS, in line with local policies, consent will be obtained from the students themselves and/or their parents/guardians (see online supplemental appendix for consent forms).

10.1136/bmjopen-2022-071353.supp1Supplementary data

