### Data management and analysis plan

During electronic data collection through Dataform (LimeSurvey),^33^ G-SHPPS data are uploaded to a secure server that will only be accessible by the city and WHO. Summary results of key indicators will be produced for each city.

GSHS data are collected on computer scannable answer sheets with no personal identifying information. Data will be processed using standard cleaning and generic data analysis programmes. A city-specific database will be generated and results will be displayed on a standard fact sheet including information on response rates, a summary of methods and weighted prevalence estimates with CIs.^15^

The Axivity AX3 data will be downloaded on-site and uploaded to a secure WHO server with unique identifiers, with no personal information. The unique identifier will be used to link these data to the student’s GSHS physical activity data. Time spent in total physical activity, moderate-to-vigorous-intensity physical activity, and in sedentary behaviour will be computed from the Axivity AX3 data for each student, using standard methods.^34 35^ Agreement between the Axivity AX3 and the questionnaire data will be assessed using approaches consistent with previous studies.^31 36^

For GSHS and G-SHPPS follow-up surveys, the same data analysis procedures as at baseline will be used.

To assess effectiveness of the interventions, comparative analysis of changes of policies and programmes and of students’ health behaviours between the intervention and control group will be undertaken. With most outcome variables being binary, most intervention effects will be estimated through adjusted ORs with 95% CIs, using random effects logistic regression to adjust for within-school clustering. Additionally, a score across multiple risk and protective behaviours will be computed for each city (depending on the selection of questionnaire modules in each city), and effectiveness of the intervention will also be tested using this score.^37^ Data analysts will be blinded to allocation of schools in the two arms.

The analysis will account for potential spillover effects as much as possible. Spillover effects are defined as benefits provided by interventions that extend beyond direct recipients and impact people in close physical or social proximity who did not directly receive the intervention themselves, namely students in the control arm.^38^

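### City-level arm effects rest on about 30 schools, and the named random-effects logistic model carries no small-sample method; the usual default gives about 6-7% two-sided type I error, not 5%

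*Protocol article*

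**What the plan says.** Under Study design and locations, the Protocol article states: "In each city, approximately 30 schools will be selected and randomly assigned to either the intervention or control group". It gives no allocation ratio.

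Under Study population and sampling, the unit of sizing is the city: "The city sample size was calculated to test the hypothesis". There, "logistic regression was selected as the statistical test", "the required power level was set at 80% and the significance level prespecified at α=0.05", and "The to-be-detected effect was specified at an OR=0.75".

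Under Data management and analysis plan, most effects are to be adjusted odds ratios with 95% CIs, "using random effects logistic regression to adjust for within-school clustering". In addition, "a score across multiple risk and protective behaviours will be computed for each city", and effectiveness is tested on that score too.

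Questionnaire modules, secondary outcomes and the interventions themselves are also chosen city by city. The article describes no analysis pooled over the four cities. It does not name the estimation method, the reference distribution or the degrees of freedom behind the CIs.

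**The concern.** Schools are randomised, so the arm effect in a city is mainly a contrast between two sets of about 15 schools. Its precision is limited by the number of schools, and roughly 3,000 students per city do not change that. Under the common default for random-effects logistic regression, two things go slightly wrong with so few clusters. Maximum likelihood tends to underestimate the between-school variance, and the Wald interval uses 1.960 where about 28 degrees of freedom would call for 2.048. Both make the interval too narrow. This is separate from any clustering by class: it remains when school is the only source of correlation.

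At stake is whether a city-level 95% CI covers 95% and a 5% test holds 5%. Many binary indicators are planned per city, so even one or two excess points per test add false positives.

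**Working it through.** **1. The plan's own figures.** The article starts from n=473 ("The initial sample size calculation resulted in n=473"). A large-sample Wald calculation for logistic regression returns exactly 473 with a two-sided 5% level, 80% power, OR 0.75, a standard normal covariate and an event probability of 0.30. The sidedness, the covariate and the probability are assumptions, because the article gives none of them. The inflation also reproduces: 473 × 1.5 / 0.9 = 788.3, and 788.3 × 4 = 3,153.3. Whether 473 is the right starting number is a separate question and is not used below.

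**2. Clusters and cluster size.** Thirty schools split equally (assumed) give 15 per arm and 30 − 2 = 28 degrees of freedom. Respondents per school are 3,153 × 0.9 / 30 = 94.6. From design effect = 1 + (m − 1) × ICC, the plan's 1.5 implies ICC = 0.5 / 93.6 = 0.0053.

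**3. Quantile alone.** t(0.975; 28) = 2.048 against z = 1.960, a ratio of 1.045, so a z-based interval is about 4.5% too narrow. The nominal 5% becomes P(|t28| > 1.960) = 6.0%.

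**4. Null simulations.** A random-intercept logistic model was fitted by maximum likelihood, with school as the only source of correlation, at follow-up only and without covariates. The table uses 2,000 runs per row (Monte Carlo SE about 0.5 points), except the pooled row with 500 (about 1.0). ICC is on the latent logistic scale.

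| Schools per arm, students per school | Prevalence | ICC | z | t, schools − 2 df | School-level t-test |
|---|---|---|---|---|---|
| 15, 95 | 10% | 0.0053 | 4.6% | 3.6% | 4.1% |
| 15, 95 | 30% | 0.0053 | 5.5% | 4.5% | 4.5% |
| 15, 95 | 10% | 0.02 | 6.9% | 5.6% | 4.8% |
| 15, 95 | 30% | 0.02 | 7.0% | 5.9% | 5.5% |
| 15, 95 | 10% | 0.05 | 7.7% | 6.8% | 5.6% |
| 15, 95 | 30% | 0.05 | 7.1% | 6.2% | 5.3% |
| 15, 47 (one age group) | 30% | 0.02 | 6.2% | 5.1% | 4.8% |
| 60, 95 (four cities) | 30% | 0.02 | 5.4% | 5.2% | 4.8% |

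Two further sets used 15 v 15 schools, 95 students each and prevalence 20%:
- 3,000 runs per setting, ICC on the proportion scale from 0.0053 to 0.05: z 6.4-6.6%, t 5.3-5.7%.
- 5,000 runs per setting: z 6.8% at ICC 0.03 and 6.6% at ICC 0.05, t 5.6% at both.

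**5. Why the results differ at ICC 0.0053.** The design-effect formula works on the proportion scale. A latent ICC of 0.0053 is a school variance of 0.0053 / 0.9947 × π²/3 = 0.0175. On the proportion scale this is about 0.0175 × p(1 − p): 0.0016 at 10% prevalence and 0.0037 at 30%. The design effects are then about 1 + 93.6 × 0.0016 = 1.15 and 1 + 93.6 × 0.0037 = 1.35. The first two rows therefore have less clustering than the plan's 1.5. The proportion-scale runs, which match 1.5, put the error within 6.4-6.6%.

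**The case against.** The strongest objection is that the article nowhere commits to an uncorrected interval. Random-effects logistic regression is compatible with t-based degrees of freedom, a bias-reduced variance or a permutation p-value, and a full protocol or analysis plan not shown may specify one. This stands, and it makes the point conditional. A reader might infer that the reported CIs will be too narrow; the text does not establish that. The point is still worth raising because the article fixes the model and the interval at a number of clusters where the software default matters.

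Second, fitting the odds ratios city by city is an inference. The sizing, the score, the modules and the interventions are set by city and no pooled analysis is described, so it is the natural reading, but the sentence on odds ratios does not say it. With 60 schools per arm the simulated error was 5.4%, so a pooled analysis has no evident problem.

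Third, a reader might conclude that the 5% level is exceeded for every indicator in every city, or that the error favours false claims of benefit. Neither is supported. The excess depends on ICC and prevalence, and one low-ICC setting gave 4.6%. Narrow intervals do not shift the estimate, so in a two-sided test with equal arms the excess falls about equally on benefit and harm.

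Fourth, the simulations compare arms at follow-up only, while the article also speaks of differential change from baseline. In an arm-by-time contrast the stable school effect largely cancels and school-by-period variation takes its place. The percentages cannot be carried over to that analysis, although its between-school information still comes from about 30 schools.

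**Conclusion.** The point holds in a limited form. If city-level arm effects are fitted by maximum likelihood with normal-quantile Wald intervals, two-sided type I error is about 6-7% in most simulated settings (range 4.6% to 7.7%), so coverage is typically about 93-94%. At the ICC implied by the plan's design effect of 1.5, taken on the proportion scale with 20% prevalence, the excess is still about one and a half points.

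This rests on equal allocation of about 30 schools, about 95 respondents per school, school as the only level of clustering, a follow-up comparison without covariates, and the assumed ICCs and prevalences. The simulations concern binary indicators; they were not run for the multi-behaviour score. The defect is modest. It is worth fixing because the remedy is nearly free and the validity of the CIs should not depend on how large the ICC turns out to be for each indicator.

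**What to change.** Add a sentence to Data management and analysis plan stating that city-level arm effects use a small-sample method. Either of these would do:

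- t with number of schools minus 2 degrees of freedom, together with a bias-reduced variance estimate. The t quantile alone is not quite enough: it left 3.6% to 6.8% in the 15-per-arm simulations.
- A test that re-randomises schools within city, following the allocation procedure actually used, with the random-effects odds ratio kept as the estimate. This holds 5% by construction.

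Apply the same rule to the city-level score and, if differential change is the estimand, to the arm-by-time contrast. State also the allocation ratio and whether the odds ratios are fitted within city. If a correction is already specified elsewhere, a reference to it is enough.

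The cost is wording only, with no new data. CIs widen by about 5% on the log-odds scale (2.048 / 1.960 = 1.045). By normal approximation a test with 80% power at z falls to about 77.5% (1.960 + 0.842 − 2.048 = 0.754, Φ(0.754) = 0.775), and slightly further with the variance correction. The article says that analysts are blinded to allocation, so the choice should be fixed before unblinding.

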### Patient and public involvement statement

Relevant local stakeholders will be engaged at all project stages to ensure that this research builds local capacity and is responsive to the health needs and priorities of the students in each city.^39^ Besides representatives of the national or local health and education authorities and local researchers, the study committees include community and school stakeholders. Student participants, parents/guardians, teachers and community leaders will lead the use of the collected survey data to identify and implement interventions. Interventions will additionally be shaped by pictures that students provide of what they perceive as facilitators and barriers to their own health behaviour.

### Trial status

This trial began recruitment in January 2022. Baseline data collection started in the first city (Jaipur; India) in August 2022 and has been finalised in all four cities in May 2023. After the 2-year intervention period and the follow-up assessments, the study completion date is expected in January 2026. WHO as the trial management body will provide oversight to this multicity trial throughout its duration.

## Ethics and dissemination

The master protocol and the four site-specific protocols have been approved by the WHO Research Ethics Review Committee (ERC.0003397). The four site-specific protocols have also been approved by the Jodhpur School of Public Health’s Institutional Review Board for Jaipur, India; the Noguchi Memorial Institute for Medical Research Institutional Review Board for Sekondi-Takoradi, Ghana; the Ministry of Health and Wellness’ Advisory Panel on Ethics and Medico-Legal Affairs for St Catherine, Jamaica, and the Comité d’éthique pour la recherche biomédicale of the Université Mohammed V of Rabat for Fez, Morocco. Following standard G-SHPPS procedures, permissions from all schools to take part in the study will be obtained prior to field work. For the GSHS, following standard procedures previously used in over 100 countries, all parents/guardians will be notified about the study and parental/guardian consent will be obtained following local laws and policies. For the physical activity validation study, all parents/guardians will be notified and parental/guardian consent and/or student assent will be obtained in each city, adhering to local laws and policies.

The present study is minimally intrusive on the student’s privacy, on schools and communities. All data collection tools have previously been tested and used in populations similar to the target population of this study. Through participatory planning and careful review, it will be ensured that the interventions are of minimal physical, psychological and social risk. It is expected that the target population will benefit from the outcome of the interventions, in the form of improved policies and practices, as well as improved behavioural outcomes. In each city, local stakeholders will determine appropriate compensation for participating students’ time spent at the data-to-action workshop and to co-design interventions.

Following GSHS and G-SHPPS policy, data will be held at the country level, with a copy at WHO, for an initial 2-year period. During this time, each site will be encouraged to produce any report and publication they desire. After this period, data sets will be made publicly available, including in the WHO NCD microdata repository.^40^ GSHS and G-SHPPS results will be presented in a summary report, including user-friendly infographics, for sharing with the participating students, their parents, teachers and communities. Data and results from the physical activity validation study will be stored on a WHO server and will be made available to interested researchers on request after the initial 2-year period.
